## Abstract

**Background:**

Endophenotypes are heritable markers, which are more prevalent in patients and their healthy relatives than in the general population. Recent studies point at disturbed regulation of the hypothalamic-pituitary-adrenocortical axis as a possible endophenotype for depression. We hypothesize that potential endophenotypes for depression may be affected by selective serotonin re-uptake inhibitor antidepressants in healthy first-degree relatives of depressed patients. The primary outcome measure is the change in plasma cortisol in the dexamethasone-corticotrophin releasing hormone test from baseline to the end of intervention.

**Methods:**

The AGENDA trial is designed as a participant, investigator, observer, and data-analyst-blinded randomized trial. Participants are 80 healthy first-degree relatives of patients with depression. Participants are randomized to escitalopram 10 mg per day versus placebo for four weeks. Randomization is stratified by gender and age. The primary outcome measure is the change in plasma cortisol in the dexamethasone-corticotrophin releasing hormone test at entry before intervention to after four weeks of intervention. With the inclusion of 80 participants, a 60% power is obtained to detect a clinically relevant difference in the primary outcome between the intervention and the placebo group. Secondary outcome measures are changes from baseline to four weeks in scores of: 1) cognition and 2) neuroticism. Tertiary outcomes measures are changes from baseline to four weeks in scores of: 1) depression and anxiety symptoms; 2) subjective evaluations of depressive symptoms, perceived stress, quality of life, aggression, sleep, and pain; and 3) salivary cortisol at eight different timepoints during an ordinary day. Assessments are undertaken by assessors blinded to the randomization group.

**Trial registration:**

Local Ethics Committee: H-KF 307413

Danish Medicines Agency: 2612-3162.

EudraCT: 2006-001750-28.

Danish Data Agency: 2006-41-6737.

ClinicalTrials.gov: NCT 00386841

## Background

Robins and Guze described five phases in the development of a valid classification of psychiatric illness: clinical description, laboratory studies, delimitation from other disorders, follow-up studies and family studies [1]. Later, response to treatment was added as a sixth phase [2]. Recently, the endophenotype concept has emerged as a strategic tool in neuropsychiatric research [3].

Endophenotypes are quantifiable components in the "genes-to-behaviours" pathways distinct from psychiatric symptoms [3]. In parallel with the classification of psychiatric diseases, endophenotypes are validated by specificity, state independence, heritability, familial association, co-segregation, and biological and clinically plausibility [4].

Several possible endophenotypes have been proposed in affective disorders, including stress regulation, cognition, neuroticism, depression and anxiety symptoms [4]. Pharmacological anti-depressants may have an effect on endophenotypes in healthy persons with a family history of depression. We hypothesized that treatment response could be added to the validation of possible endophenotypes for depression. However, a systematic search for randomized multiple-dose, placebo-controlled trials on the effect of selective serotonin reuptake inhibitors did not identify any trials in which healthy first-degree relatives of depressed patients received a selective serotonin re-uptake inhibitor for at least one week (unpublished data).

### Possible endophenotypes for depression

#### Hypothalamus-pituitary-adreno-cortical (HPA) axis regulation

Impaired regulation of the HPA axis during an acute episode of depression is the most consistent laboratory finding [5-7]. The combined dexamethasone (DEX)-corticotrophine releasing hormone (CRH) test is a sensitive test for detecting altered HPA axis regulation [8]. In this test, the stimulating effects of 100 μg CRH on corticotrophin (ACTH) and cortisol are examined under the suppressive action of 1.5 mg of dexamethasone. ACTH and cortisol in the combined DEX-CRH test demonstrated an exaggerated response in patients with depression compared to healthy controls with a family history of depression [9] and between healthy first-degree relatives of patients with depression compared to healthy controls without a family history of depression [9]. Increased ACTH and cortisol in the combined DEX-CRH test therefore seems to be a promising biomarker for depression and a potential endophenotype for depression [10].

#### Cognition

Alterations in cognitive functions are common and included in the diagnostic criteria for depression [11] and some patients experience cognitive dysfunction even in euthymic phases of the disease [12-16]. A high-risk study showed impairment of selective and sustained attention, executive function, language processing and working and declarative memory in subjects with a family history of depression as compared to participants without [17]. Thus cognitive function may be a candidate endophenotype for affective disorders.

#### Personality

Neuroticism is a measure of an individual's tendency to experience negative emotions that are manifested at one extreme as anxiety, depression, and moodiness, and at another extreme, as emotional stability. Neuroticism is most frequently measured by questionnaires such as Eysenck Personality Questionnaire (EPQ) [18] and the revised NEO Personality Inventory (NEO-PI-R) [19]. The heritability of neuroticism is well established [20]. Studies of healthy first-degree relatives of patients with a depression point at neuroticism as an endophenotype for depression [21].

#### Other potential endophenotypes for depression

More than 90% of depressed patients complain about impairment of sleep quality, which has been suggested as a potential endophenotype for depression [22]. The effect of antidepressants on sleep quality in healthy individuals with a family history of depression has not been investigated. Subjective measures of stress, aggression, pain, and quality of life are all factors known to improve with remission of depressive symptoms. Whether this is a direct effect of treatment with antidepressants or a consequence of improvement in depressive symptoms is unclear.

### Proportion of possible endophenotypes for depression

Based on results from recent studies it is estimated that 30% of healthy persons with a family history of depression will exhibit at least two of the three possible endophenotypes: dysregulation of the HPA axis, cognition, and neuroticism [23]. The prevalence of other possible endophenotypes is unknown.

### The effect of antidepressants on endophenotypes for depression

Treatment with antidepressants in patients with an acute depression is associated with partial normalization of the HPA axis [24,25], enhanced cognitive function [26], and reduction in the personality trait of neuroticism [27]. In these trials it has not been possible to distinguish the treatment effect on the endophenotypes from the treatment effect on the disease, since remission of depressive symptoms is associated with partial normalization of the endophenotypes. It is not known whether the treatment responses on the disease symptoms are mediated through an effect on the endophenotypes or vice versa. Results of recent randomized, placebo-controlled trials suggest that antidepressants have an effect on psychological variables and behaviour in individuals without psychiatric illness [28-30], one of these studies did not mention the family history status of the included individuals [28] but in two of the studies [29,30] healthy individuals with a family history of psychiatric illness were excluded.

In summary, no trial has investigated the effects of antidepressants on possible endophenotypes in healthy individuals with a family history of depression.

### Genotyping

A recent systematic review and meta-analysis of pharmacogenetic studies of antidepressant response suggests that polymorphisms in genes such as 5-HTTLPR, STin2, HTR1A, HTR2A, TPH1, and BDNF may modulate antidepressant response [31], but the association between gene polymorphisms and the effect of an antidepressant treatment on the putative endophenotypes for depression has not been explored.

### Objectives

With the AGENDA trial (**A**ssociations between **G**ene-polymorphisms, **E**ndophenotypes for **D**epression and **A**ntidepressive Intervention) we want to test the hypothesis that potential endophenotypes for depression are affected by intervention with an antidepressant in healthy first-degree relatives of patients with the diagnosis of depression.

## Methods

The AGENDA trial is designed as a participant, investigator, observer, and data-analyst-blinded randomized trial in which participants receive either escitalopram 10 mg or placebo for a period of four weeks (Figure 1).

**Figure 1 F1:**
[figure not shown]
**Flowchart for The Agenda Trial**.

### Study organization

The study is conducted at the Department of Psychiatry, Rigshospitalet, Copenhagen University Hospital, Denmark as part of the Centre for Pharmacogenomics, University of Copenhagen. The trial has a data monitoring and safety committee (DMSC) that is independent of the investigators conducting the trial.

### Participants

Participants are recruited as healthy first-degree relatives of patients with a diagnosis of depression given at discharge from psychiatric hospital in- or out-patient contact [32]. These patients participated in ongoing studies at the psychiatric department of Rigshospitalet, University of Copenhagen, Denmark. Individuals meeting the inclusion criteria and none of the exclusion criteria are enrolled in the trial (Appendix 1). The exclusion criteria were chosen partly for safety reasons and partly to decrease the risk of results being confounded by factors known to substantially affect the HPA-axis, thus interfering the primary outcome measure. Women taking birth control pills were instructed to discontinue these 6 weeks prior to entering the trial. All women were carefully instructed to use double barrier birth control methods and pregnancy tests were performed both before and after the intervention.

### Interventions

The participants are randomized to receive either escitalopram or placebo by oral administration as a single dose of 10 mg each evening as self-medication at home for four weeks. On completion of four weeks of double-blind intervention (or early discontinuation from the trial) participants entered a five-day blinded down-titration period to nil medication. Escitalopram 10 mg was selected because of its specific serotonergic selectivity [33] and because of the favourable adverse reaction profile [34], thus facilitating blinding. The dose of escitalopram 10 mg for four weeks was estimated to have a sufficient effect, since effect on depressive symptoms in patients with a major depression is observed within one to four weeks as compared with placebo [34]. The validity of the results depends on a high compliance and high completion in the trial. This was sought obtained by weekly telephone control calls to the enrolled participants to insure adherence to the protocol and to record adverse events. Escitalopram and placebo tablets were identical in appearance, colour, smell, and solubility allowing for blinding of treatment assignment. H. Lundbeck A/S provided identically appearing blister packages containing escitalopram or placebo. An independent pharmacist then packed, sealed and numbered the drug packages according to a randomization list provided and concealed by the Copenhagen Trial Unit (CTU), Centre for Clinical Intervention Research, Rigshospitalet.

### Randomization

Randomization into one of the two intervention groups is done immediately after it has been established that the participant fulfils all the inclusion criteria and none of the exclusion criteria. Randomization is stratified by age (18 – 31 years and 32 – 60 years) and sex in order to get an equal distribution in the intervention groups, knowing that the response to the DEX-CRH test is sensitive to these factors. Participants are randomized in a 1-to-1 ratio to receive escitalopram 10 mg or placebo. The Copenhagen Trial Unit (CTU), Centre for Clinical Intervention Research, Rigshospitalet performs the centralised randomization, and only the IT Manager of the CTU will know the block size used for stratification. The sponsor-investigator (UK) provides information of the participants to the CTU during the entry assessment as soon as participation in the study has been decided. CTU performs the computer-generated randomization to ensure adequate allocation concealment and adequate generation of the allocation sequence [35]. The number of the allocated treatment is communicated to UK, both by phone and email.

### Blinding

All study personnel and participants are blinded to the packaging of the study drug, and blinding is maintained throughout monitoring, follow-up, data management, assessment of outcomes and data analyses. The randomization code will not be broken until all the data has been analysed and conclusions drawn. At the assessment after four weeks intervention, every participant, the sponsor-investigator (UK), and the neuropsychological testers will make a guess as to which intervention the participant has received. When the trial is finished, inter-rater reliability between the actual intervention and the guesses will be estimated to assess the degree to which blinding has been successful.

### Outcome assessments

Outcomes are assessed at entry and after four weeks intervention by assessors who are all blinded to the randomization group.

Depression has a wide range of possible features that can be measured and tested as possible endophenotypes [36]. Since no prior trial has investigated the effect of SSRI on healthy first-degree relatives of patients with depression, we have chosen to include many outcomes since the nature of this trial is predominantly exploratory, i.e., hypothesis generating, and only partly hypothesis testing. When available, previously developed and validated scales and instruments were used in order to facilitate appropriate comparisons with data obtained in previous studies.

### Primary outcome

During selection of the primary outcome, it was stressed that the outcome should be objective and of clinical importance. Further, blinding should be possible at all levels of assessment and analyses. The measurement of change in plasma cortisol in the DEX-CRH test from entry before to four weeks during intervention fulfils these criteria. Plasma cortisol will be estimated as the total area under the curve (AUC-total) from administration of CRH at 15.00 hours to the last plasma cortisol measure at 18.00 hours. The DEX-CRH test is performed according to international standards with a few minor modifications [9]; thus plasma cortisol, plasma ACTH and salivary cortisol are measured at the same time points.

### Secondary outcomes

Secondary outcomes include changes in scores from baseline to four weeks on: 1) cognitive functions are measured with a broad battery of neuropsychological tests with relevance in relation to depression, evaluating memory, attention, visuomotor speed, visuo-constructional abilities, decision making, logical thinking, executive functions, verbal fluency, social and moral cognition, recognition of emotions and emotional intelligence [37-54], 2) neuroticism as measured by the NEO-PI-R [19] and EPQ [18].

### Tertiary outcomes

Tertiary outcomes include changes in scores from baseline to four weeks on: 1) mood as measured by the Hamilton rating scale for depression (HAM-D17) [55] and the Hamilton rating scale for anxiety (HAM-A14 [56], 2) participants subjective perception of pain on a visual analogue scale modified from Klepstad [57], 3) sleep on a visual analogue scale for sleep quality, sleep items from the HAMD-17 and supplementary questions on sleep characteristics, 4) aggression by The Buss-Perry Aggression Questionnaire [58], 5) depressive symptoms by the Beck Depression Inventory (BDI-21) [59], 6) quality of life by the WHO Quality of Life questionnaire [60], 7) a global measure of stress by the Cohen Perceived Stress Scale [61], and 8) salivary cortisol assessed by Salivettes during an ordinary day in the participants usual environment at the following time points: awakening, awakening + 15 min., awakening + 30 min., awakening + 45 min., awakening + 60 min., 12:00, 18:00 and at 23:00 [62]. Further, side-effects are assessed at four weeks by the UKU Side Effect Rating Scale [63].

### Genotyping

Blood samples are stored in a bio bank for further analyses. Among others we intend to genotype for the 5-HTTLPR-short/long-promoter variant, and the catechol-O-methyltransferase (COMT), and to test whether these genotypes will be associated with the response to escitalopram on the potential endophenotypes for depression. Further, messenger RNA for the glucocorticoid receptor will be analysed and associated to the effect of escitalopram.

### Assessments

Participants are subjected to almost identical sequences of assessments at entry and after four weeks of intervention (Appendix 2). The first part of the assessment is a telephone interview, and the individuals who are not excluded at that time point, are scheduled to meet at the clinic at two different days before and following four weeks of intervention with escitalopram or placebo. At the first day of examination the participants are interviewed to evaluate fulfilment of inclusion and exclusion criteria including the Schedules for Clinical Assessment in Neuropsychiatry (SCAN) [64] and various socio-demographics.

### Sample size

A high-risk study performed by Modell et al. [9] found that healthy high-risk probands of patients with a diagnosis of depression examined by the DEX-CRH test present with a cortisol AUC-total (mean ± SEM) of 15,064 ± 3,947 nmol × min/L. Further, Modell et al reported that cortisol AUC-total (mean ± SEM) in healthy individuals with no family history of depression was 7,773 ± 1,071 nmol × min/L. A clinically relevant effect of escitalopram on the cortisol AUC-total (mean ± SEM) was thus estimated to be the difference in cortisol AUC-total (mean ± SEM) of high-risk probands of patients with the diagnosis of depression and that of healthy individuals with no family history of depression. Accordingly, the relevant difference we aim to detect or reject is 15,064 – 7,773 = 7,291 nmol × min/L. Given a standard deviation (SD) = SEM × √14 = 3,947 × 3.7 = 14,768 nmol × min/L provides a power of the trial at a minimum of 60% (1 - β = 0.60), β being the risk of overlooking a difference in the cortisol AUC-total. However, the power in the trial may be higher, considering the use of analysis of covariance (ANCOVA) of the change from entry to after four weeks of intervention in AUC total during the DEX-CRH test. Based on these calculations we aim for a full data set of 80 participants to be able to conclude in relation to the primary outcome measure.

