## Results

### Current trial status

Enrolment started July 2007 and is ongoing until July 2009. Status in May 2009 is that 390 eligible persons have been screened and that 77 of these have been randomized (Figure 1) and the dataset is complete for 64 participants regarding the primary outcome measure.

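### The 60% power is called a minimum, but it is the value at 80 complete datasets and an SD of 14,768, and the planned analysis does not secure it as a floor

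*Protocol article*

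**What the plan says.** The Sample size section of the Protocol article sets the target by comparing two groups in a cited high-risk study: "the relevant difference we aim to detect or reject is 15,064 – 7,773 = 7,291 nmol × min/L". The SD comes from the high-risk group in that study: "SEM × √14 = 3,947 × 3.7 = 14,768 nmol × min/L". From these it concludes that the trial "provides a power of the trial at a minimum of 60" per cent. It adds that ANCOVA of the change could raise the power, and ends: "we aim for a full data set of 80 participants to be able to conclude in relation to the primary outcome measure".

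The Abstract (Methods) gives the same power on a different basis: "With the inclusion of 80 participants, a 60% power is obtained to detect a clinically relevant difference".

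Statistical methods analyses each participant's before-after difference, first unadjusted and then adjusted for covariates that reach p < 0.1 univariately. Table 1 lists AUC-total plasma cortisol among the covariates for the primary outcome. Missing primary data are multiply imputed, and the imputed result prevails if the two disagree. Current trial status (May 2009, enrolment still open) reports 77 randomized and that "the dataset is complete for 64 participants regarding the primary outcome measure".

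**The concern.** A minimum should hold under every analysis and every level of completeness that the plan allows. This one depends on two conditions that the text does not attach to it.

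- **The SD.** The calculation uses the between-person SD of one AUC. The SD of a change score differs from this, and is larger when the two measurements correlate weakly.
- **The N.** Included and complete participants are the same number only if no data are missing.

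What is at stake is how a non-significant result is read. The section says that it aims to detect or reject 7,291. A reader who takes 60% as guaranteed may treat a non-significant result as having rejected a normalising effect, when the data may be compatible with both no effect and the full target effect.

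**Working it through.** **Inputs.** Difference 7,291, SD 14,768 and N = 80 (Sample size); 1:1 allocation (Randomization), so 40 per arm; α = 0.05 (Statistical methods). Sidedness is not stated. Two-sided is assumed because it reproduces 60%, whereas one-sided gives 71.3%.

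**The plan's own figure.** 3,947 × √14 = 14,768. (The printed factor 3.7 would give 14,604; the SD shown uses the unrounded root.) The standard error is 14,768 × √(2/40) = 3,302, and 7,291 / 3,302 = 2.208. Normal approximation: Φ(2.208 − 1.960) = 59.8%. Two-sample t test (noncentral t, 78 df): 58.7%. So 60% is reproduced, as a rounded point value.

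**Which SD applies.** Let ρ be the correlation between the entry and four-week AUC, with equal variance at both times. Then:
- unadjusted change: SD = 14,768 × √(2(1 − ρ)), which exceeds 14,768 when ρ < 0.5;
- ANCOVA with baseline AUC in the model: residual SD = 14,768 × √(1 − ρ²), which never exceeds 14,768.

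The document gives no ρ, so the values below are an assumed range. Power by t test:

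| ρ | SD of change | Change, 80 complete | ANCOVA, 80 complete | Change, 64 complete | ANCOVA, 64 complete |
|---|---|---|---|---|---|
| 0 | 20,885 | 34% | 59% | 28% | 49% |
| 0.3 | 17,474 | 45% | 63% | 38% | 53% |
| 0.5 | 14,768 | 59% | 71% | 49% | 61% |
| 0.7 | 11,439 | 80% | 86% | 71% | 78% |

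**Completeness.** 64/77 = 83%, and 83% of 80 is about 66. At SD 14,768, power by t test is 49% with 64 complete and 51% with 66.

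**Detecting or rejecting 7,291.** The 95% CI half-width is t × SD × √(2/n per arm). With 80 complete and SD 14,768 it is 6,574. The target is then excluded only if the observed reduction is below 7,291 − 6,574 = 717, and the result is significant only if the reduction exceeds 6,574. Anything between 717 and 6,574 neither detects nor rejects the target.

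**The case against.** **The arithmetic is sound and ANCOVA supports the word minimum.** The section points to ANCOVA, and Table 1 lists AUC for the primary outcome (taken here as the baseline value). With baseline AUC in the model, the single-measurement SD is the worst case over ρ, so about 59–60% is a true floor on the correlation at 80 complete. The p < 0.1 filter would also rarely remove it. Under equal variances the correlation of change with baseline is −√((1 − ρ)/2), or −0.59 at ρ = 0.3 and −0.39 at ρ = 0.7. With 80 participants p < 0.1 needs only about 0.185 in absolute size (1.665/√(1.665² + 78)). This argument stands for the adjusted result. It does not cover the unadjusted result, which the plan lists first and does not rank below the adjusted one.

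**The low power is disclosed.** The document prints 60%, defines β, and calls the trial predominantly exploratory. That is fair. The defect is the unconditional wording, not concealment.

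**Three stronger readings are tempting, and the documents do not support them.**
- A reader might infer that the trial's power is really 49%. But 64 of 77 is an interim count with enrolment open, and some of the other 13 may still have been in their four weeks. The 49% also ignores any gain from baseline adjustment or from imputation using ACTH and salivary cortisol.
- A reader might infer that 58.7% is the best the design can do. The ANCOVA columns show otherwise.
- A reader might infer that even an observed difference of zero could not exclude 7,291. With 64 complete the half-width is 7,380, just above the target, but with 66 it is 7,263, just below. The claim turns on two participants, and modest baseline adjustment also reverses it.

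**Conclusion.** The point holds in a limited form. The 60% is correct as a point value for 80 complete datasets when the SD of the analysed quantity is 14,768. It is not secured as a minimum, for two reasons.

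- For the unadjusted change, power is at least about 59% only if ρ ≥ 0.5, and runs from 34% to 80% as ρ goes from 0 to 0.7. The adjusted analysis would supply the floor, but the plan neither guarantees baseline AUC a place in the model nor says which result is primary.
- The Abstract ties the figure to 80 included and the Sample size section to 80 complete. If only 64 to 66 were complete, power would be about 49–51% at SD 14,768. That is a scenario, not a forecast.

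These figures assume a two-sided 0.05 test, equal variances at the two visits, and the plan's SD. The ANCOVA floor is a floor on the correlation only. It does not protect against missing data or against an SD that was misjudged from a group of 14. This is a correction of wording and of the analysis hierarchy, and does not invalidate the design.

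**What to change.** 1. In Sample size, replace the minimum with: *about 59–60% with 80 complete datasets if the SD of the analysed quantity is 14,768*. Add power over a range of correlations and of completeness. Make the Abstract refer to 80 complete datasets too.
2. In Statistical methods, name the ANCOVA with baseline AUC always included as the primary analysis, not subject to the p < 0.1 filter. This makes about 59–60% a floor on the correlation at 80 complete.
3. State that 7,291 counts as rejected only if the 95% CI excludes it, and that a non-significant result is otherwise inconclusive.

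The cost is a few restated figures, one sentence on the model and one on interpretation. The headline power becomes conditional and slightly less favourable. No extra enrolment or unblinding is needed.
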